### Outcome Measurements

The participants in the intervention group will complete the assessments at (1) the baseline (T0); (2) at the end of the first counseling session (T1); (3) at the end of the second counseling session (T2); (4) at the end of the third counseling session (T3); and (5) 3 months after the third counseling session (T4). There will be a week interval between the counseling sessions (T1, T2, and T3). Meanwhile, the participants in the control group will be measured at 3–5 points in time depends on the number of counseling sessions they have. They will fill the questionnaires at (1) the baseline (T0); (2) at the end of their counseling session(s), (T1 and/or T2 and/or T3, etc.); and (3) 3 months after the last session (TX). The data will be collected using the online forms and will be assisted by the research assistants.

The primary outcome of the proposed study will be CSE measured by the Coping Self-Efficacy (CSE) Scale. The Indonesian version of the CSE consists of 26 items with 11-point scale (0–10). The scale has good reliability (*r* = 0.92), (Nurhidayah, 2020). The total score will be used as an indicator of the level of CSE of participants. The CSE is defined as a belief about own ability of an individual to perform specific coping behavior (Chesney et al., 2006). Self-efficacy serves as evidence in measuring changes in the coping ability of individuals, especially for those who seek professionals to solve their problems (Chesney et al., 2006; Yoo et al., 2020).

The secondary outcomes of this study will be (1) resilience and (2) level of depression. Resilience is defined as the capacity of a dynamic system to adapt successfully to adversity that threatens system function (Masten, 2014). The Resilience Scale (RS-14), (Surzykiewicz et al., 2019), which will be used to measure this variable, has five dimensions, namely, equanimity, perseverance, self-reliance, meaningfulness, and existential aloneness. The short version of the RS test has been adapted to the Indonesian language. It has 14 items with a 7-point Likert scale (*r* = 0.87). The scale has good Construct Validity Fitness Indexes [Non Normed Fit Index (NNFI) = 0.99, Root Mean Square Error of Approximation (RMSEA) = 0.027, and Standardized Root Mean Residual (SRMR) = 0.026], (Valentino, 2021).

The PHQ will be used to measure the level of depression. The Indonesian version of this scale has nine items with a 4-point Likert scale (*r* = 0.80), (Onie et al., 2020). Similar to other scales, the PHQ-9 is a self-report questionnaire. The total score will be used as a cutoff score in the initial screening. A total score of 15 or higher indicates moderate and severe major depression that can be an indicator for initiating a drug treatment (Arroll et al., 2010). The students with a PHQ-9 score of 14 or lower will be included in this study. The results from this scale will also serve as the secondary outcome of this study.

The demographic data of participants will also be collected using the form. Some of the data will be used by the counselors for intervention purposes (e.g., family, educational, and organizational background) while the rest will be used only for research purposes (e.g., gender, ethnicity, age, University level, and university major).

The main researchers will develop a data management form, and the research assistants will input all the data. The identities of participants will be coded to maintain confidentiality. The data management form also has a password, which is known only by the researchers.

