## Materials and Methods

### Study Design

This study describes a study that will be conducted as a two-armed parallel randomized controlled non-inferiority trial. The trial is in line with the guidelines for the protocol content of the non-inferiority trial (Piaggio et al., 2012). It will also be based on the guidance of the Standard Protocol Items: Recommendations for Intervention Trials (SPIRIT) Statement (Tetzlaff et al., 2012; Chan et al., 2013). The non-inferiority scheme will be used in this study because the application is not aimed to be more powerful or effective than the usual treatment but aimed to increase the practicality of the counselors to store the data in the application and to hide personal contacts (e.g., email addresses or online meeting IDs) by solely using the application only for the counseling purposes (Hahn, 2012).

To eliminate the assay sensitivity, bias, and constancy assumption (ABC) of this non-inferiority trial, there are several things included in the design. First, the outcome measurement tools that will be used in both groups are reliable. Second, besides using randomizing in allocation and double-blinding procedure, the control group will get the TAU without any intervention to prevent a bias. Third, the data will be collected in the same period for both groups to minimize any situational effects, such as the COVID-19 pandemic-related government policies in this country (Walker, 2019).

The proposed study will be a parallel group design comparing two types of treatments. The intervention group will use the application whereas the control group will get the TAU. The intervention group will have three counseling sessions for a month; meanwhile, the control group will have many sessions based on the need of each individual. All outcomes will be assessed repeatedly using online self-reported forms, which will be facilitated by research assistants. The assessments will be taken (1) before the intervention, (2) after each session (a session/week), and (3) after 3 months. The study design is shown in Figure 1.

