### Data Analysis

Descriptive statistics will be used to describe relevant demographic data, such as the frequency and the percentage for the categorical data as well as the mean and the SD for the outcome measurements. There will be three analysis plans to prove the non-inferiority of the application, which are (1) repeated-measures ANOVAs (Goodman et al., 2016; Twisk et al., 2018), which will be used to test for differences between the TAU and the intervention groups (i.e., between-subjects factor) in the treatment at the four time points (i.e., within-subjects factor). We would like to assess whether the outcomes will be improved after treatment using the application and the TAU. An analysis will be conducted to check the constancy assumption. Then, both (2) the intention-to-treat (ITT) and (3) the per-protocol analysis will be performed. Previous studies showed that performing both analyses will produce more convincing results to conclude the non-inferiority of a new treatment (Hahn, 2012; Walker, 2019). The ITT analyses will be chosen to handle the missing value due to the protocol deviations, withdrawal, and non-compliance (Gupta, 2011) whereas the per-protocol analysis will minimize the factors that would make the two groups seem similar (Walker, 2019).

The statistical hypotheses in this non-inferiority trial use Δ. The null hypothesis states that the intervention using the application will be inferior to the TAU (H0: TAU–SAENA ≥ Δ). The alternative hypothesis states that the intervention will not be inferior (will have a similar effect) to the TAU although the effect may not be as good as the TAU within the extent of margin (H1: TAU–SAENA < Δ). Of note, 95% CI will be used. The interval will be the mean difference between the outcome measures of the two groups. The formula is as follows:

$$\begin{array}{l} \left(\mu_{saena}-\;\mu_{TAU}\right)\pm 1.96\sqrt{\frac{\sigma_{saena}^{2}}{n_{saena}}+\frac{\sigma_{TAU}^{2}}{n_{TAU}}} \end{array}$$

μ, mean; Tau, standard deviation; *n*, sample.

The 1.96 is the *z*-value, and the value from this formula can now be compared with Δ. If the interval remains above Δ, then the inferiority of the application will be proven according to the standards that have been set. In contrast, if the upper limit for treatment difference by the intervention group compared to the TAU group is < Δ, then the non-inferiority will be concluded.

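### TAU assessments exist only for the sessions each student has, so the planned repeated-measures time factor, and any T2 or T3 comparison, cannot include all randomised students

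*Protocol article*

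**What the plan says.** **SAENA schedule.** Study Design: "The intervention group will have three counseling sessions for a month". Outcome Measurements: "There will be a week interval between the counseling sessions (T1, T2, and T3", with the last assessment "3 months after the third counseling session (T4". With baseline, that makes five assessments for every student.

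**TAU schedule.** Study Design: "the control group will have many sessions based on the need of each individual". Outcome Measurements: "the participants in the control group will be measured at 3–5 points in time depends on the number of counseling sessions they have". These are a baseline, an assessment at the end of each session the student has (the list is left open after T3), and a last one "3 months after the last session (TX".

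**Analysis.** Data Analysis plans a repeated-measures ANOVA that compares the groups "in the treatment at the four time points (i.e., within-subjects factor". Non-inferiority is then judged by a 95% confidence interval for the difference between two group means. No time point is named for that interval.

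**Safeguard.** Among the design features meant to protect the non-inferiority comparison, Study Design states that "the data will be collected in the same period for both groups to minimize any situational effects".

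**The concern.** In the SAENA arm the assessment schedule is fixed. In the TAU arm, whether a T2 or T3 measurement exists depends on how many sessions the student turns out to need, which is determined after randomisation and may be related to the outcome. The time factor is then not the same factor in both arms, and at T2 and T3 the TAU group is a selected subset of those randomised.

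In a non-inferiority trial such selection can make SAENA look acceptable when it is not, or the reverse. It is also a rule about data collection: a form tied to a session that never took place is never sent, and no later analysis plan can recover it. The intention-to-treat rationale under Data Analysis covers values lost through deviations, drop-out and poor adherence. It does not cover assessments that were never scheduled.

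**Working it through.** **1. Which assessments exist.** Assumptions: weekly sessions in both arms, the first in week 1, and 3 months taken as 13 weeks. Weeks count from the start of counselling. Outcome Measurements fixes the weekly interval only when describing SAENA; Study Design mentions one session a week without tying it to an arm.

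| Student | Assessments | Count | Week of last assessment |
|---|---|---|---|
| SAENA | T0, T1, T2, T3, T4 | 5 | 3 + 13 = 16 |
| TAU, 1 session | T0, T1, TX | 3 | 1 + 13 = 14 |
| TAU, 2 sessions | T0, T1, T2, TX | 4 | 2 + 13 = 15 |
| TAU, 3 sessions | T0, T1, T2, T3, TX | 5 | 3 + 13 = 16 |
| TAU, 8 sessions (outside 3–5 points) | T0, eight session forms, TX | 10 | 8 + 13 = 21 |

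The 3–5 points correspond to 1–3 sessions. The open-ended list in the same section, and the unlimited sessions in Study Design, do not fit that limit.

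**2. Fitting four levels.** A one-session TAU student has three measurements and cannot fill four levels, however they are chosen. If the levels are T0–T3, two-session students also lack T3 and the 3-month assessment is left out. If they are T0, T1, T2 and the 3-month point, SAENA's end-of-treatment measurement is left out.

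**3. Who enters the confidence interval at each possible time.**
- T1: all SAENA students; TAU students with at least one session.
- T2: all SAENA students; TAU students with at least two.
- T3: all SAENA students; TAU students with at least three.
- 3 months: everyone in both arms, at weeks that differ as in the table.

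**4. Size of the timing difference at 3 months.** Within 3–5 points it is at most 16 − 14 = 2 weeks, with TAU earlier. Assume the outcome drifts 0.01–0.03 SD per week, 30% of TAU students have one session and the rest three. The mean gap is then 0.30 × 2 = 0.6 weeks, which is 0.006–0.018 SD, or 3–8% of a margin of 0.22. The drift and the 30% are assumptions.

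**5. The plan's own sample size.** n per arm = 2σ²(z₁₋α + z₁₋β)²/Δ². With σ = 1, Δ = 0.24, one-sided α = 0.05 and 80% power: 2 × (1.645 + 0.842)²/0.24² = 214.8, so 215, as stated. The analysis uses a 95% two-sided interval (z = 1.96), so power with all 215 per arm is:
- SE = √(1/215 + 1/215) = 0.0964
- Φ(0.24/0.0964 − 1.96) = 70%

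**6. Illustrative loss of power.** If 30% of TAU students (assumption) have fewer than three sessions and a complete-case analysis drops them, TAU n is about 150:
- SE = √(1/150 + 1/215) = 0.1064
- Φ(0.24/0.1064 − 1.96) = 62%

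For assumed shares of 10% and 50% the result is 68% and 53%. At one-sided 0.05 the 30% case goes from 80% to 73%. With Δ = 0.22, the margin stated in the section on determining the margin, it goes from 63% to 54% at z = 1.96.

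**7. Illustrative bias at T3 or in complete cases.** Let s be the share of TAU students with fewer than three sessions and ρ the correlation between stopping early and a better outcome. The mean of the remaining TAU students shifts by −ρφ(c)/(1 − s), with c = z₁₋ₛ. For s = 0.30 and ρ = 0.2: −0.2 × 0.348/0.7 = −0.099 SD, or 41% of 0.24. The type I error is Φ(0.099/0.1064 − 1.96) = 15% instead of 2.5%. Over s = 10–50% and ρ = 0.1–0.3 the shift is 0.02–0.24 SD (8–100% of 0.24) and the type I error is 4–53%. If ρ is negative the shift changes sign and works against SAENA. The documents give neither s nor ρ.

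**The case against.** Several points on the other side stand.

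- **The 3-month assessment.** A reader might infer that TAU students are also lost selectively at 3 months. They are not: TX is scheduled for every TAU student, including those with one session. It has the same anchor as T4, 3 months after the last session, and measuring from the end of treatment is a recognised choice.
- **The timing gap.** A reader might take the unlimited TAU sessions literally and compute a large gap, such as 21 − 16 = 5 weeks at eight sessions. That requires 10 assessments, which the 3–5 points exclude, and an arm-level gap of that size would require TAU to average eight sessions. Larger gaps remain possible if sessions are uncapped or spaced differently, but no figure is given.
- **Complete cases.** Nothing in the article says that incomplete series are deleted, and the handling of missing values may be set out in an analysis plan not shown. The confidence interval itself does not need complete series.
- **Direction of bias.** It is tempting to say that TAU's early successes drop out and SAENA is favoured. The article says only that sessions follow need. Students may also stop because they are dissatisfied, which would reverse the direction.
- **Same period.** The stated purpose of that safeguard is to limit situational influences such as pandemic policy, that is, to run the arms over the same calendar period. A difference of up to 2 weeks does not defeat it.
- **Four points.** Four does fit a two-session TAU student, and T0–T3 is a coherent treatment-phase reading for SAENA.

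None of this supplies the T2 and T3 measurements that are never taken for some TAU students, gives a one-session student a fourth level, or names the time point of the interval.

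**Conclusion.** The plan is wrong as written on this point. In-treatment measurement in one arm depends on a post-randomisation variable, the stated ANOVA cannot be run on all randomised students, and the non-inferiority interval has no named time point. The three sections disagree on the number of assessments, and Study Design and Outcome Measurements disagree on whether TAU sessions are limited. This rests on the text alone.

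The consequences are less certain. There is no by-design loss at 3 months, and timing there differs by at most about 2 weeks if sessions are weekly and the 3–5 points hold. The fall in power from about 70% to about 62% assumes complete-case analysis and a 30% share; the 70% itself reflects a separate mismatch between the sample-size error level and the 95% interval. A T3 or complete-case comparison favours SAENA if students who are doing better stop TAU early, and disfavours it if the opposite holds. The documents do not settle which.

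**What to change.** Send the same online forms to both arms at the same times counted from randomisation, whatever the number of sessions attended: for example weeks 1, 2 and 3 and one fixed follow-up week, about week 16. Name one of these common time points as primary for the non-inferiority interval. Reconcile Study Design, Outcome Measurements and Data Analysis so that all three give the same number and list of time points, and so that the statements on TAU session numbers agree. Report the number of sessions descriptively.

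The cost is protocol wording and a changed form-sending schedule; the forms are already online and supported by research assistants, and counselling in either arm need not change. The change must come before data collection, because forms not sent cannot be recovered. One small downside is that some TAU students may still be in counselling at the fixed follow-up. An assessment 3 months after the last session can be kept as secondary.

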### Determining an Inferiority Margin of the Trial

In the non-inferiority trial, the researchers need to determine Δ (Hahn, 2012). In this study, the margin is the maximum acceptable extent of non-inferiority of the mobile-based counseling application. The maximum limit of Δ can be set to the entire effect size of the active control treatment (Hahn, 2012). Several proposals for choosing the inferiority margins in the context of SFBT have been made (Table 1). There are several suggestions for the maximum difference in outcomes that will be considered clinically irrelevant. It ranges from *d* = 0.17 to *d* = 1.76. The smallest margin was suggested by Schmit et al. (2016), (*d* = 0.24) for the treatment of internalizing disorders. Thus, in this study, it was decided to use the inferior margin of 0.22 (i.e., the inferior margin up to 0.22), corresponding to a small effect size.

**Table 1 T1:** The effect size from the solution-focused brief therapy (SFBT)-related studies.

**Previous studies**	**Effect size**
Impacts on academic and emotional difficulties (Daki and Savage, 2010)	≈0.13 (partial eta squared, medium effect size)
Meta-analysis of solution-focused brief therapy for treating symptoms of internalizing disorders (Schmit et al., 2016)	≈0.24 (Hedges' g, small effect size)
Examining the effectiveness of solution-focused brief therapy: a meta-analysis (Kim, 2008)	0.26–0.38 (Cohen's *d*, small effect size)
SFBT for health-related psychosocial outcomes (Zhang et al., 2018)	0.34 (Cohen's *d*, small effect size)
Solution-focused brief therapy in schools: A review of the outcome literature (Kim and Franklin, 2009)	0.38–1.76 (Cohen's *d*, medium to large effect size)

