### Participants

The target population in the study will be University students who have academic-related psychological problems. The inclusion criteria of the sample are a University student, aged 18–25 years old, having academic-related problem(s), and registering as a participant in this study. The academic-related problems that will be included in the study are (1) (educational) adjustment difficulties; (2) difficulties in writing a thesis; (3) academic procrastination; (4) poor self-regulation for learning; and (5) a low grade point average (GPA). The study will exclude students with (1) physical disabilities; (2) under the care of mental health professionals; and (3) the score of PHQ-9 more than 14 (having severe depression), (Rahmadiana et al., 2019).

The participants of the study will be those who register in a University counseling center. They will be then screened with the PHQ-9. If they are willing to participate in the study, the research assistants will give informed consent and the right to withdraw from the study at any given time they wish to. The students who decline to join the study or withdraw from the study will be followed up to identify their reasons for declining and withdrawing from the study. The students have a right to undergo post-trial treatment if needed.

The sample size is a sensitive issue in the non-inferiority trial (Hahn, 2012). Large sample size is usually needed. However, if the new intervention is assumed to be slightly more effective than the TAU, the number of samples can be reduced. The mobile-based counseling application can be assumed to be more practical for the students in this country. Those who live remotely can still access the psychological services. The data from the University counseling center in 2020 were also a source of consideration in determining the sample size. The center admitted 482 clients in that year, with an average of 40 clients per month. With 80% CI, the expected SD will be one, and the inferiority margin (Δ) will be 0.24. It was calculated that the number of participants per arm needs to be 215 and the total sample size needs to be 430.

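### The non-inferiority margin is 0.24 in the sample size but 0.22 in the margin section, and the decision rule gives no number

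*Protocol article*

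**What the plan says.** Three sections of the protocol article bear on the margin.

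- **Participants (sample size):** "the expected SD will be one, and the inferiority margin (Δ) will be 0.24". The result is 215 per arm, 430 in total. The 80% figure is worded as a confidence level: "With 80% CI, the expected SD will be one".
- **Determining an Inferiority Margin of the Trial:** "it was decided to use the inferior margin of 0.22 (i.e., the inferior margin up to 0.22), corresponding to a small effect size". Just before this, the section says of candidate margins "It ranges from *d* = 0.17 to *d* = 1.76", and then names 0.24, from a meta-analysis of solution-focused brief therapy (SFBT) for internalizing disorders, as the smallest. It also states a ceiling: "The maximum limit of Δ can be set to the entire effect size of the active control treatment".
- **Data Analysis:** the hypotheses and the decision rule are written with the symbol Δ only. On the interval: "Of note, 95% CI will be used".

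Table 1 lists effects of SFBT, which is the approach behind the app's counseling protocol. The article gives no effect size for treatment as usual (TAU), which is the control.

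**The concern.** In a non-inferiority trial the margin is the decision rule. Two values of it, with no number where the test is defined, leave the rule open. For the hypotheses as written (TAU minus SAENA), an upper limit between 0.22 and 0.24 SD passes one section and fails another. On the SAENA minus TAU interval that the section prints, this is a lower limit between −0.24 and −0.22. Unless the matter is settled beforehand, the margin could be chosen after the result is known.

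The sample size also depends on it. The Discussion maintains that the trial, though limited in numbers, has enough power, and that statement holds or fails with the margin used.

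Finally, the reasoning behind the margin cannot be followed. The lower end of the stated range conflicts with the value called smallest, the move to 0.22 is not explained, and the ceiling refers to a treatment whose effect is not given.

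**Working it through.** **Inputs.** Δ = 0.24 and SD = 1 (Participants); Δ = 0.22 (margin section); 215 per arm (Participants); 95% CI, hence one-sided 2.5% (Data Analysis). Assumptions: the 80% is power; the true difference is 0, because no number is given; the sample-size paragraph states no alpha, so I tried several.

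**1. Reproduce the plan's figure.** n per arm = 2(z₁₋α + z₀.₈₀)² / Δ².

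- Δ = 0.24, one-sided 5%: 2(1.645 + 0.842)² / 0.24² = 214.7, so **215**. This is an exact match.
- Δ = 0.24, one-sided 2.5%: 273. One-sided 10%: 157.
- Δ = 0.22, one-sided 5%: 2(1.645 + 0.842)² / 0.22² = 255.5, so 256. One-sided 2.5%: 325. One-sided 10%: 187.

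No combination tried with 0.22 gives 215, so the trial was sized on 0.24.

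**2. Power at 215 per arm.** SE = √(2/215) = 0.09645. Power = Φ(Δ/SE − z₁₋α), with 0.24/0.09645 = 2.488 and 0.22/0.09645 = 2.281.

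| Δ | One-sided 5% (z = 1.645) | 95% CI (z = 1.96) |
|---|---|---|
| 0.24 | Φ(0.843) = 80.1% | Φ(0.528) = 70.1% |
| 0.22 | Φ(0.636) = 73.8% | Φ(0.321) = 62.6% |

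Changing the margin alone costs 80.1 − 73.8 = 6.3 points at one-sided 5%, or 70.1 − 62.6 = 7.5 points with the 95% CI. The remainder of the drop from 80% to 63% comes from the confidence level.

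**3. How often the two values disagree.** The same differences give the probability that a trial with no true difference ends between the margins: about 7.5% with the 95% CI.

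**4. The derivation.**

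- The range starts at 0.17, but 0.24 is called the smallest. Both cannot hold.
- 0.17 is not in Table 1. The only smaller entry there, 0.13, is a partial eta squared labelled medium, which is on another scale.
- 0.22 follows 0.24 with no intermediate step, and the parenthesis presents it as an upper bound where a fixed value is needed.
- The ceiling is the active control's effect. Table 1 covers SFBT only, so compliance cannot be verified from this text.

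**5. Units.** Δ rests on "the expected SD will be one", so it is in SD units. The Data Analysis formula is a plain difference in means, and the CSE total runs from 0 to 260 (26 items scored 0 to 10). A bare 0.22 inserted there would be read as scale points.

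**The case against.** The strongest reply is that the 215 is correctly computed, that 0.22 and 0.24 are close, and that a condensed article need not describe TAU or every step of the margin's derivation.

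Much of this stands. There is no arithmetic error in the 215. The full protocol may describe TAU and its effect, so the article's silence does not show that TAU differs from SFBT. The contradiction between the two margins remains, however. It is not an omission that another document could fill, because the article states both values.

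Two stronger readings are tempting, and the article does not support either.

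- **That the margin breaks its own ceiling.** No number is given for the control's effect. Against 0.24, which the article calls smallest, 0.22 lies below and 0.24 lies exactly on it, which the ceiling's wording permits. A breach appears only if 0.17 is taken as the ceiling, and the article never says that.
- **That a calculable share of the control's effect would be retained.** Any such percentage, or a second criterion built on it, treats an SFBT effect as the TAU effect. The article gives no ground for that.

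Nor does the article rest improvement on the margin alone: Data Analysis plans a separate repeated-measures look at change in both groups. With no untreated group, that is weak evidence of efficacy, but it is planned.

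**Conclusion.** The point holds as an internal contradiction on the number that decides the trial, and it must be fixed. The sample size uses 0.24, the margin section decides on 0.22, and the test names neither. At 215 per arm, power is 80% or 74% at the one-sided 5% level that reproduces the plan, and 70% or 63% with the stated 95% CI. These figures assume SD 1, no true difference, 80% read as power, and no dropout. A true advantage for SAENA would raise them, but the article puts no number on one.

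The derivation is inconsistent about its smallest value and leaves 0.22 unexplained. Whether the margin respects its ceiling is unverifiable from this text, which is less than saying that the ceiling is exceeded.

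**What to change.** Before any outcome data are seen:

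1. State one numeric Δ in the Participants, margin and Data Analysis sections. I suggest 0.22, because the margin section decides on it and it is the stricter value. Remove the parenthesis that turns it into an upper bound, and give the reason for 0.22.
2. Say that Δ is in SD units. For the comparison in Data Analysis, either convert it to CSE points (0.22 × a pre-specified SD) or standardise the difference.
3. Restate the power of 215 per arm for that Δ and the 95% CI: about 63% with no true difference. Reaching 80% would need 325 per arm.
4. Source the 0.17 or remove it, and cite evidence on the control's effect if the ceiling is to be invoked.
5. Limit the conclusion to SAENA being not worse than TAU by more than Δ.

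The cost is wording plus a less favourable power statement. Enlarging the trial is a separate and dearer choice: 325 per arm is 650 participants, and the centre admitted 482 clients in 2020.
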